## Study design and methods

### Design

The self-help IMI called *CANreduce 3.0* will be evaluated within a three-arm RCT, which will compare a mindfulness-based self-help IMI (arm 1); a CBT-based self-help IMI (arm 2); and a waiting-list control condition (arm 3) in their effectiveness reducing cannabis use among frequent cannabis users. Since the mindfulness-based self-help IMI (arm 1) contains newly-developed contents, testing its effectiveness is of primary interest in the current RCT. The CBT-based self-help IMI (arm 2) is a slightly-adapted version of CANreduce 2.0 [19] and serves as a reference program [52]. Performance of the reference intervention is, thus, not the main consideration; however, if the test (arm 1) and reference intervention (arm 2) both fail to demonstrate a statistically-significant advantage over the control condition, this could suggest that the trial is insensitive, or lacks assay sensitivity. If differences are observed, the difference between the reference intervention (arm 2) and controls can be used to help assess the practical relevance of the difference between arm 1 and the control condition [52].

Consistent with this, a confidence interval approach will be used as an exploratory tool to identify similarities between treatment arms 1 and 2 [53, 54]. The control condition (arm 3) will consist of all the same assessments administered to the other two subject groups (see Section Measures), as well as brief advice on the health risks of cannabis use (e.g., potential short-term and long-term effects). Some screening and brief internet interventions from Swiss addiction counselling also are available on the Internet and, as such, might be accessed by controls, but no links to them will be provided in CANreduce 3.0. Participants who are assigned to the control group will be offered the opportunity to receive the intervention delivered in study arm 1 after they complete the final assessment of the RCT, six months after they register for the study).

The trial has been registered with the ISRCTN registry (date of registration: 09/09/2021) and is traceable as ISRCTN14971662 (http://www.isrctn.com/ISRCTN14971662). It also has been approved by the Ethics Committee of the Faculty of Arts and Social Science at the University of Zurich, Switzerland (approval number: 20.4.17). Any important protocol modifications would be reported to this Ethics Committee.

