### Hypotheses

The following detailed study hypotheses for the main outcome (i.e., reduction in the monthly days of cannabis use between baseline and the 3- and 6-month follow-up assessments) will be tested:A mindfulness-based self-help IMI for the reduction of cannabis use (study arm 1) is more effective than being on a waiting list (control condition, study arm 3).A CBT-based self-help IMI for the reduction of cannabis use (study arm 2) is more effective than being on a waiting list (control condition, study arm 3).A mindfulness-based self-help IMI for the reduction of cannabis use (study arm 1) is at least as effective as a CBT-based self-help IMI (study arm 2).

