### Data analyses

Data will be analyzed according to the ITT principle. Multiple imputation procedures, using the R package *mice* [87], will be used to address missing data. *mice* involves specifying a multivariate distribution for the missing data and drawing imputations from their conditional distributions by Markov chain Monte Carlo (MCMC) techniques. We intend to use 20 imputed data sets, as this has been deemed sufficient [87]. The imputation model will include all primary and secondary outcomes (see above). Adjunct variables, like sociodemographic data, will be included if they improve convergence within the imputation model.

Differences in primary and secondary continuous outcome variables between the two active study arms (1 and 2) at baseline and at both follow-up points will be tested using linear mixed models (LMM). The LMMs will be specified to model clusters and repeated measures by defining random effects for study condition and time (repeated measures). Appropriate distributions for non-normal continuous outcomes will be specified (e.g., negative binomial, zero-inflated). In addition to the ITT analyses, per-protocol analyses will be performed.

To investigate the exploratory research question of whether study arm 1 (mindfulness-based self-help IMI) results in a similar reduction in days of cannabis use as study arm 2 (CBT-based self-help IMI), a confidence interval approach will be used for the ES of the difference between these two study arms, using a two-sided 0.05 level of significance [54]. The equivalence margin is a priori set at d = 0.20, corresponding to the smallest value that would constitute a relevant effect [88]. The upper bound of the 95% CI for the ES will be compared against the predefined equivalence margin of d = 0.20 and must be below the margin to show equivalence.

Additional exploratory regression analyses will be conducted to determine whether baseline variables predict the frequency or quantity of cannabis use, severity of dependence (SDS), reduced psychiatric symptoms (PHQ-9, GAD-7), perceived stress (PSS-10) and mindfulness (MAAS) at 3 and/or 6 months follow-up, treatment retention, and adherence. For these analyses, we will use linear, multinomial, or binary regression models, depending on the scale used for the outcome measure. Treatment retention and client satisfaction will be compared between study arms one and two by Pearson chi-square analysis at week 6 (intervention end).

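### The arm 1 versus arm 2 rule checks only the upper confidence bound of an effect size with no stated direction, so it is not an equivalence rule; with the direction fixed it is a non-inferiority rule that fits hypothesis 3

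*Protocol article*

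**What the plan says.** All references are to the protocol article.

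- **Question.** Data analyses asks whether arm 1 "results in a similar reduction in days of cannabis use as study arm 2". Design describes the same comparison in these words: "a confidence interval approach will be used as an exploratory tool to identify similarities between treatment arms 1 and 2".
- **Margin and interval.** "The equivalence margin is a priori set at d = 0.20". The interval is built "using a two-sided 0.05 level of significance", so it is a 95% interval.
- **Decision rule.** "The upper bound of the 95% CI for the ES will be compared against the predefined equivalence margin", and that bound "must be below the margin to show equivalence". Nothing is required of the lower bound.
- **Direction.** The quantity is called only "the ES of the difference between these two study arms". No section gives the order of subtraction, the meaning of the sign, or a statement that the absolute value is used.
- **Hypothesis.** Hypothesis 3, in the list of hypotheses for the main outcome that are to be tested, is that arm 1 "is at least as effective as a CBT-based self-help IMI (study arm 2)".
- **Scale.** Under Measures, the primary outcome is days of cannabis use in the preceding 30 days, where lower is better. Hypotheses words the main outcome as a reduction in monthly days, where higher is better.

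**The concern.** Equivalence is a two-sided claim: neither arm differs from the other by more than the margin in either direction. A check on one bound rules out a difference in one direction only, which is a non-inferiority criterion. Even that holds only if the bound checked is on the side where the test arm is worse.

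The article has two problems here. The label does not fit the rule, since one bound cannot support a claim of equivalence or similarity. And because the sign of d is open, the reader cannot tell which one-sided claim the rule supports. The sign could also be settled after the data are seen.

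The conclusion about arm 1 versus arm 2 is at stake. This is the only rule the article gives for hypothesis 3. The status of that hypothesis also varies: Hypotheses lists it with the others to be tested, while Design and Data analyses treat the comparison as exploratory.

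**Working it through.** The article gives no power or precision figure for arm 1 versus arm 2. Its only power figure (above 80%, Power analysis) concerns arm 1 versus arm 3 and is not at issue, so there is nothing of the plan's own to reproduce first.

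**Inputs.** n = 210 per arm (Power analysis); margin 0.20 and a 95% interval (Data analyses). Assumption made here: a simple two-sample approximation for a standardised difference, SE(d) = √(2/n), without baseline adjustment, repeated measures or imputation.

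**Step 1: precision.**
- SE(d) = √(2/210) = 0.0976
- 95% half-width = 1.96 × 0.0976 = 0.191

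**Step 2: what passes.** The rule is met when d + 0.191 < 0.20, that is, when the observed d is below 0.20 − 0.1913 = 0.0087. There is no lower limit. An observed d of -0.50 has the interval -0.50 ± 0.19, or -0.69 to -0.31. That lies wholly beyond -0.20, yet its upper bound is below +0.20, so the rule declares equivalence. More generally, any interval lying entirely below zero passes automatically, so a trial can find a significant difference between the arms and equivalence at the same time.

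**Step 3: how often.** P(rule met) = Φ((0.0087 − δ)/0.0976) for true difference δ. The both-bounds column is the chance that the whole 95% interval lies within ±0.20.

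| True d | Rule in the article | Whole interval below 0 | Both bounds within ±0.20 |
|---|---|---|---|
| +0.20 | 2.5% | 0.0% | 0.9% |
| -0.20 | 98.4% | 53.6% | 0.9% |
| -0.30 | 99.9% | 86.7% | 0.06% |
| -0.50 | 100% | 99.9% | 0.0% |

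For example, at δ = -0.30: (0.0087 + 0.30)/0.0976 = 3.16, and Φ(3.16) = 0.999. In the negative direction, the further apart the arms are, the more certain the rule is to call them equivalent.

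**Step 4: what this means under each sign.**
- *d = days of use, arm 1 minus arm 2 (positive = arm 1 worse).* The negative rows are a superior arm 1, so superiority is labelled equivalence. The +0.20 row shows that a true deficit equal to the margin passes in 2.5% of trials, which is the usual one-sided non-inferiority error. The calculation is valid for hypothesis 3; only the name is wrong.
- *d = reduction in days, arm 1 minus arm 2 (positive = arm 1 better).* The negative rows are an inferior arm 1, so a clearly worse arm 1 is labelled equivalent, contrary to hypothesis 3.

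**Step 5: sensitivity to attrition.** The article expects relatively large drop-out but gives no rate. Assuming 30% or 50% loss (147 or 105 per arm), P(rule met) at δ = -0.30 is 99.0% or 95.2%. The logic does not depend on the sample size.

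**The case against.** The strongest reply is that the intended sign can be inferred. Measures states the primary outcome as days of use, and Power analysis uses a negative interaction coefficient (-0.069, reduced to -0.06), which reads as benefit being negative. On that scale, with arm 1 minus arm 2, positive d means arm 1 is worse and the upper-bound check is the standard non-inferiority test of hypothesis 3. The estimate and interval would be computed in any case, and the two active arms are also compared by mixed model, so a superior arm 1 would not be hidden. The comparison is exploratory.

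Much of this stands. The one-sided calculation is not wrong in itself, and the reading that passes an inferior arm 1 is possible but not shown to be intended. It is not far-fetched, though: Hypotheses words the main outcome as a reduction, and Data analyses uses the same word when it poses the question the rule is to answer. What does not stand is the label. Under the favourable sign, the rule still calls a clearly better arm 1 equivalent.

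Three stronger inferences are tempting and are not supported:
- *That two arms which both fail against the waiting list would simply be reported as equivalent.* Design already says that such a result could mean the trial lacks assay sensitivity. A formal gate on arm 2 beating arm 3 is a preference for an exploratory comparison; its absence is not an error.
- *That the margin is too wide because it equals the 0.20 reported for CANreduce 1.0 and exceeds the 0.11 for earlier digital interventions.* Arm 2 is a slightly adapted CANreduce 2.0, and the Background gives d = 0.60 against the waiting list for the support-team arm of that version. The margin is one third of that (0.20/0.60), although arm 2 now uses an eCoach.
- *That the trial is too small for this comparison.* It was sized for arm 1 versus arm 3, and low power in an exploratory comparison is not a fault in the plan.

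**Conclusion.** The point holds. The article states a complete decision rule for equivalence that has no lower bound and no direction, and no other section supplies either. At 210 per arm, any observed d below about +0.009 passes. Under one sign a clearly superior arm 1 is called equivalent; under the other a clearly inferior one is, in 99.9% of trials at a true d of -0.30.

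A reader might infer that the plan will pass off an inferior arm 1 as equivalent in nearly every trial. The documents do not support that: the figure needs d on the reduction scale, whereas Measures and Power analysis point to days of use, where the same arithmetic is a sound non-inferiority test. The established defects are the wrong label, the undefined sign and the inconsistent status of hypothesis 3.

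The probabilities rest on the unadjusted two-sample approximation. A mixed model, multiple imputation or drop-out would change them but not the logic. Severity is moderate: the comparison is exploratory, and the main arm 1 versus arm 3 comparison and the sample size are unaffected.

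**What to change.** 1. In Data analyses, define d as days of cannabis use, arm 1 minus arm 2, so that positive means arm 1 is worse.
2. Call the upper-bound rule (upper 95% bound below 0.20) a non-inferiority criterion. It then tests hypothesis 3 with no change to the calculation.
3. Use the word equivalent, or similar, only if the whole 95% interval lies within -0.20 to +0.20. This should supplement the non-inferiority criterion and not replace it, because a clearly better arm 1 satisfies hypothesis 3 but would fail a two-sided rule.
4. Mark hypothesis 3 as exploratory in Hypotheses, in line with Design and Data analyses.

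The cost is a few sentences, with no change to data collection, sample size or the main analysis. The downside is that a claim of equivalence becomes harder to make.

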### Measures

Table 3  provides an overview of all measurements and when in the study they are used. All measurements are self-reported, assessed online, and detailed subsequently:*Sociodemographic data* include age, gender, sexual orientation, educational attainment, financial situation, and migration background.Problematic cannabis use is assessed with the revised version of the *Cannabis Use Disorders Identification Test (CUDIT-R* [68]*;)*. Each of the eight items contains a statement about cannabis use that must be answered on a 5-point Likert scale that ranges from "never" (0) to "daily or almost daily" (4). The total score ranges from 0 to 32 with scores of 8 or more indicating hazardous cannabis use and scores of 12 and more indicating a possible CUD.Various further aspects of cannabis use are assessed. Regarding *consumption patterns: (3a)* the i) number of years using cannabis, ii) means of consumption (oral, smoking or vaporizing), and iii) number of days using CBD over the last 30 days are measured. Participants then *define their personal standard joint (3b)* by selecting between i) indoor, outdoor, and resin, ii) mixed with or without tobacco, and iii) six different quantities of the substance, varying between 67 and 500 mg. Each of the resulting 36 combinations is illustrated with a photo of an unrolled joint paper on which the specific amount of cannabis (and tobacco) that has been selected by the participant is displayed. A ruler beside the unrolled joint serves as a reference. This standard joint is used as a quantitative unit to assess 3c) the frequency and quantity of cannabis use in the last seven days, in accordance with the *Time-Line-Follow-Back (TLFB)* method [69, 70].The *Severity of Dependence Scale (SDS)* is a five-item scale that can be used to screen for dependence. Each item must be answered on a 5-point Likert scale that ranges from 0 to 4. Total scores range from 0 to 20, with a score of 4 or more indicating cannabis dependence [71].The *short version of the Alcohol Use Disorders Identification Test (AUDIT-C* [72]*;)* is a screening tool with three items that assess problematic and risky alcohol consumption. All items must be answered on a 5-point-Likert scale, that ranges from 0 to 4. The total score ranges from 0 to 12, with scores of 3 (women) and 4 (men) indicating problematic use and scores of 4 (women) and 5 (men) or more indicating risky use.The *NIDA ASSIST* is an *Alcohol, Smoking and Substance Involvement Screening Test (ASSIST) from the National Institute on Drug Abuse (NIDA).* We only use the pre-screener [73] without the items on alcohol and tobacco. For each drug, consumption is rated, ranging from "never" (0) to "daily or almost daily" (4).Drug Abuse Screening Test (DAST-10) is an instrument with ten yes–no questions about drug abuse [74]. Each answer is allocated either 0 or 1 point, leading to a total score between 0 and 10. Scores are interpreted as follows: 0 for no problem, 1–2 for a low level, 3–5 for a moderate level, 6–8 for a substantial level, and 9–10 for a severe level of abuse.The *Perceived Stress Scale (PSS-10)* is an instrument with 10 statements about experiences of unpredictable, uncontrollable, and overwhelming life events. Answers range from "never" (0) to "very often" (4), leading to a total score between 0 to 40 with higher numbers indicating more stress, but without distinct any cut-offs for diagnostic purposes [75, 76].The *Patient Health Questionnaire for Depression (PHQ-9)* consists of nine items that assess degree of depression. Answers range from "not at all" (0) to "almost daily" (3), resulting in a total score between 0 and 27 [77]. A score of 10 or higher is considered indicative of a major depressive disorder [78].*The Generalized Anxiety Disorder Screener (GAD-7)* is a screener with seven items on anxiety symptoms, with answers ranging from "not at all" (0) to "almost daily" (3) and total scores between 0 and 21; any score of 10 or higher is considered indicative of a generalized anxiety disorder [79].The Adult ADHD Self-Report Scale (ASRS-V1.1) is a six-item questionnaire on attention deficit and hyperactivity, with answers ranging from "never (0) to "very often" (4), leading to a total score between 0 and 24 [80]. Total scores range from 0 to 24 with values of 14 and above indicating a positive screening result for ADHD [81].*The Mindfulness Attention Awareness Scale (MAAS)* is a questionnaire with 15 statements about everyday experiences in mindfulness, with answers ranging from "almost always" (1) to "almost never" (6), and higher mean scores indicating greater mindfulness [82, 83].*The Comprehensive Inventory of Mindfulness Experiences (CHIME)* is a 37-item questionnaire with answers ranging from "almost never" (1) to "almost always" (6), with higher mean scores representing more mindfulness. This relatively large instrument has eight subscales (inner awareness, outer awareness, acting with awareness, acceptance, decentering/non-reactivity, openness, relativity, and insight) and covers all aspects of mindfulness employed in current mindfulness scales [84].*Previous experience with meditation* is assessed with two questions about frequency (never, once, sometimes, regular) and guidance (innately learned, self-taught from books, learned in a course, guided by an app).*The Client Satisfaction Questionnaire for Internet Interventions (CSQ-I)* is specifically designed to assess client’s satisfaction with internet health interventions. It consists of eight items with answers ranging from "disagree" (1) to "agree" (4), leading to scores between 8 and 32; higher scores indicate higher levels of satisfaction [85].*Negative effects* of internet interventions are assessed according to Rozental [86]. Participants are asked if they have experienced any negative side effect that they attribute to the program. If so, they are asked to describe it and rate the severity of any resulting impairment.*Use of any services besides CANreduce*, like online counseling, drug counseling, general practitioner, psychologist, or psychiatrist. Participants are asked to respond ‘yes’ or ‘no’ to all of these services and to list any other unlisted services used.*Adherence and Retention:* Adherence is operationalized as average completion rate spanning the eight modules, with module completion rate defined as the highest page number visited divided by the highest page number available in a given module. Retention is operationalized as the average completion rate of the weekly consumption diary over the six-week program.

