
**Table 3 Tab3:** Overview of all measures and their measurement time points

	**Assessment instruments**	**Base-line (t**_**0**_**)**	**6 weeks (t**_**1**_**)**	**3 months follow-up (t**_**2**_**)**	**6 months follow-up (t**_**3**_**)**
1	Socio-demographics (age, gender, sexual orientation, educational attainment, migration background, financial situation)	X			
2	Cannabis Use Disorders Identification Test (CUDIT-R)	X	X	X	X
3	*Cannabis use*				
3a	Consumption Patterns (Years of Use, 30-day point prevalence of cannabis and CBD abstinence, Type of Consumption)	X	X	X	X
3b	Defining the personal standard joint	X			
3c	TLFB (Cannabis use frequency and amount for the last 7 days in standard joint units)	X	X	X	X
4	Severity of Dependence Scale (SDS)	X	X	X	X
5	Short version of the Alcohol Use Disorders Identification Test (AUDIT-C)	X		X	X
6	National Institute on Drug Abuse *Screening (NIDA ASSIST)*	X		X	X
7	Drug Abuse Screening Test (DAST-10)	X			
8	Perceived Stress Scale (PSS-10)	X	X	X	X
9	Patient Health Questionnaire for Depression (PHQ-9)	X		X	X
10	Generalized Anxiety Disorder Screener (GAD-7)	X		X	X
11	Adult ADHD Self-Report Scale (ASRS-V1.1)	X			
12	Mindfulness Attention Awareness Scale (MAAS)	X	X	X	X
13	Comprehensive Inventory of Mindfulness Experiences (CHIME)	X			
14	Previous experience in meditation (no official instrument)	X			
15	Client Satisfaction Questionnaire for Internet Interventions (CSQ-I)		X^a^		
16	Negative effects, according to Rozental et al. (2015)		X		
17	Use of any services besides CANreduce			X	X
18	Adherence and Retention^b^		X		

^a^ Only for study arms 1 and 2

^b^ Adherence and retention are constructs measured indirectly and not part of a questionnaire

The primary study outcome is the number of days of cannabis use over the preceding 30 days.

Secondary outcomes are quantity and frequency of cannabis use over the last seven days’; scores for the SDS, AUDIT-C, NIDA-ASSIST, PSS-10, PHQ-9, GAD-7, MAAS, and CSQ-I., and any negative effects attributed to the program.

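### The chi-square test named for week-6 retention and client satisfaction does not fit either measure, since both are defined as numeric scores without categories

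*Protocol article*

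**What the plan says.** The last sentence of Data analyses in the protocol article fixes the test: "Treatment retention and client satisfaction will be compared between study arms one and two by Pearson chi-square analysis at week 6", which is the end of the intervention.

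The Measures section defines the two variables:

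- Retention: "Retention is operationalized as the average completion rate of the weekly consumption diary over the six-week program". Each participant therefore has a value between 0 and 1.
- CSQ-I: eight items scored 1 to 4, "leading to scores between 8 and 32; higher scores indicate higher levels of satisfaction". That allows 25 possible values.

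No cut-off or band is given for either. The same section does give cut-offs or bands for CUDIT-R, SDS, AUDIT-C, DAST-10, PHQ-9, GAD-7 and ASRS. After Table 3, the CSQ-I is listed among the secondary outcomes as a score: "scores for the SDS, AUDIT-C, NIDA-ASSIST, PSS-10, PHQ-9, GAD-7, MAAS, and CSQ-I., and any negative effects attributed to the program".

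The sentence just before the chi-square sentence concerns exploratory regressions, some with retention as the outcome. There the model follows the type of variable: "we will use linear, multinomial, or binary regression models, depending on the scale used for the outcome measure".

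**The concern.** A Pearson chi-square test asks whether two arms differ in how participants fall into unordered categories. Retention and the CSQ-I are ordered numeric scores, so the named test can be run in only two ways. One is to group the scores, with a cut the article does not state. The other is to treat each observed value as its own category, which ignores that 30 is more satisfied than 20 and spreads the test over many degrees of freedom.

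The comparison has some interest. Arm 1 carries the new mindfulness content and arm 2 is the reference program, and the Discussion expects limited adherence and relatively large drop-out. What is at stake is power, and a readable estimate, for the secondary comparison of engagement and satisfaction between the two programs. A chi-square result also gives no mean difference with an interval, which is what a reader would want from an 8–32 score.

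**Working it through.** The article gives no effect size, power or expected distribution for these two comparisons, so there is no figure of its own to reproduce.

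**Inputs**

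- From the article: 210 per arm; CSQ-I from 8 to 32; retention as an average over six weekly diaries.
- Two-sided 0.05: the article states this level ("using a two-sided 0.05 level of significance") only for the confidence-interval comparison of arms 1 and 2. It is assumed here.
- Assumed: a standardized difference d = 0.30 and a roughly normal score. No drop-out figure is given, so 0%, 30% and 50% missing at week 6 (210, 147 and 105 per arm) serve as a range.

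**1. Information kept by a two-group cut.** For a normal score cut at c, with a proportion p above the cut, the efficiency relative to comparing means is φ(c)² / [p(1−p)].

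- 50/50: 0.3989² / 0.25 = 2/π = 0.64, a loss of 36%
- 70/30: 0.58
- 80/20: 0.49
- 90/10: 0.34

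The loss exceeds half only from a cut of about 80/20 outward.

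**2. Power when means are compared, d = 0.30, 210 per arm.** Φ(d√(n/2) − 1.96) = Φ(0.30 × 10.247 − 1.96) = Φ(1.11) = 87%.

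**3. Power after a median split.** The proportions above the cut are Φ(−0.15) = 0.4404 and Φ(0.15) = 0.5596, a difference of 0.1192. The null standard error is √(2 × 0.25/210) = 0.0488 and the alternative one is 0.0484. Power = Φ[(0.1192 − 1.96 × 0.0488)/0.0484] = Φ(0.49) = 69%. A simulation with integer scores truncated to 8–32 gave 68%.

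**4. Power when every value is a category.** If the table captured the whole effect, its noncentrality would be nd²/2 = 210 × 0.09/2 = 9.45. With 24 degrees of freedom (25 CSQ-I values) that gives at most 35%; simulations gave 29–31%. With 6 degrees of freedom (seven retention levels, assuming each week counts as filled or not) it gives at most 61–62%.

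**5. Range over sample size, d = 0.30**

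| Per arm | Means | Median split | 80/20 cut | 25 values, at most |
|---|---|---|---|---|
| 210 | 87% | 69% | 57% | 35% |
| 147 | 73% | 53% | 43% | 23% |
| 105 | 58% | 41% | 33% | 17% |

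**6. The same loss as sample size.** At the difference for which 210 per arm gives 80% power on means (d = 0.27), a median split has 61% power and would need 331 per arm. An 80/20 cut would need 432.

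**7. Retention.** Diary completion is unlikely to be normal, so one U-shaped illustration was simulated (beta-binomial over six weeks, assumed means 40% and 49%, 210 per arm). Power was 71% for a t-test, 74% for a rank test, 58% for chi-square on at least three weeks against fewer, and 49% for chi-square on all seven levels. These values depend on the assumed spread; in a similar set-up (means 45% and 54%), changing it moved t-test power between about 55% and 89%.

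**The case against.** Four points on the other side deserve an answer.

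**Conflict with the mixed-model rule.** A reader might infer that the chi-square sentence contradicts the rule sending continuous secondary outcomes to linear mixed models. It does not. That rule covers "Differences in primary and secondary continuous outcome variables between the two active study arms (1 and 2) at baseline and at both follow-up points". Table 3 labels only the 3- and 6-month assessments as follow-ups and shows the CSQ-I once, at week 6, with no baseline. The chi-square sentence is a separate rule for week 6.

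**Size of the loss.** A reader might infer that chi-square throws away most of the information, or that real differences would go undetected. Neither is established. A median split loses about 36%. A loss above half needs a cut of about 80/20 or more extreme, or the CSQ-I values left ungrouped, and the article commits to neither. Power of 68–69% instead of 87% is a reduction, not certain failure.

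**Detail left to another document.** A condensed article may leave category definitions to the full protocol or the analysis plan, and a chi-square test presupposes that categories exist. This is fair: missing categories alone are no finding, and nothing shows that a cut would be chosen after seeing the data. What stands is that the article does name a test, and that test does not suit the measures as the article defines them. Even well-chosen, pre-stated categories would carry the loss shown above.

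**Importance.** None of the stated hypotheses concerns satisfaction or retention, and the power analysis addresses arm 1 against arm 3 on days of use. This stands and limits the weight of the point.

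**Conclusion.** The point holds as a mismatch between test and scale. Pearson chi-square is named for two ordered numeric measures that have no stated categories. It ignores order and, for a roughly normal score, costs at least about a third of the information with any two-group cut. At the assumed d = 0.30 and 210 per arm that means about 87% power against about 68–69% at best, with less for lopsided cuts or ungrouped values. The 36% figure rests on approximate normality, and the power figures also on the assumed effect size and a two-sided 0.05 level. For retention the size depends on an unknown distribution, though the direction was the same in the illustration. The consequence is confined to secondary comparisons of arm 1 with arm 2.

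**What to change.** Replace the sentence with one that analyses each measure on its defined scale, arm 1 against arm 2 at week 6:

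- CSQ-I: linear model or t-test, reporting the mean difference with its 95% CI.
- Retention: as a proportion, by a rank test or a fractional or quasi-binomial regression.
- Chi-square: only for items that are truly categorical. If a grouped comparison is still wanted, state its categories in advance.

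The cost is one sentence. No new data, assessments or participants are needed.
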